### Inclusion criteria

3.3

Each infant will have to meet all of the following criteria to be enrolled in this study:♦Good health♦Single birth♦Gestational age ≥ 37 weeks (WHO)♦Birth weight ≥ 2500 g♦Appropriate weight at inclusion visit between P20 and P80 in accordance with the weight percentile charts of Chinese children aged 0 to 18 years^[21]^♦Aged > 4 months (120 days) and < 6 months (180 days)♦Being exclusively formula-fed (no breast milk meal) at the inclusion visit♦No gastrointestinal diseases within 1 month (CCDC)♦No use of antibiotics within 1 month (CCDC)♦Parents’ agreement to use one of the recommended infant formulas [no probiotics; if with prebiotics, galacto-oligosaccharides (GOS) < 2 g/100 g and no fructo-oligosaccharides (FOS) inside]♦Consent form signed by at least one of the parents or a legal guardian♦Parents able to understand the protocol requirements and to fill in the infant's diaries

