### Design and setting

3.1

This is a randomized, double-blind, placebo-controlled, 2-parallel-group trial, which will be conducted in the Shanghai First Maternity and Infant Hospital, Shanghai, China. Participating infants will undergo a 2-week run-in period and then be randomly allocated (at a 1:1 ratio) to receive either an oral probiotic product or an identical placebo once daily for 4 weeks, with a follow-up period of 8 weeks. Therefore, the duration of the subjects’ participation will be 14 weeks, with a total of 5 visits. Each parent who agrees to have his or her infant enrolled in the trial will sign an informed consent form; the study protocol has been approved by the Medical Ethics Committee of Shanghai First Maternity and Infant Hospital. The current study will be performed in accordance with the standards of the International Committee on Harmonization of Good Clinical Practice and the revised version of the Declaration of Helsinki.

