### Exclusion criteria

3.4

Infants meeting any of the following criteria will be excluded from the study:♦Congenital illness or malformation.♦Critical prenatal and/or postnatal disease.♦Mothers with metabolic and/or chronic disease.♦An allergic constitution and sensitive to probiotics (CCDC).♦Serious diseases, such as those of the cardiovascular, cerebrovascular, endocrine, liver, kidney, and hematopoietic systems, or mental diseases (CCDC).♦Other drugs during the administration of the study products, thus making it impossible to judge their efficacy and/or influencing the judgment of results (CCDC).♦Current or previous illnesses or conditions or interventions that could interfere with the study (affecting tolerance and/or growth), such as gastrointestinal malformations, chronic diarrhea, malabsorptive syndrome, malnutrition, congenital immunodeficiency, or major surgery, as per the investigator's clinical judgment.♦Oral antibiotic treatment at V1 visit and within 4 weeks before V1.♦Any medication or nutritional supplements (such as probiotics and prebiotics, except for infant formula) in the 4 weeks preceding the study start.♦Having ever consumed the test product.♦Medical conditions for which a special diet other than standard (nonhydrolyzed) cow's milk-based infant formula is required (such as cow's milk allergy, soy protein allergy, fish protein allergy, egg protein allergy, lactose intolerance, and galactosemia).♦Current participation or having participated in another clinical trial during the previous 4 weeks.♦Infants’ legal representatives without the psychological or linguistic capability to sign the informed consent form.♦Reasons to presume that the parents are unable to meet the study plan requirements (e.g., cannot contact the study representatives in the case of emergency, or have a drug addiction).

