### Randomization and blinding

3.5

The product allocation list will be generated using a dynamic randomization algorithm designed to minimize an imbalance between the 2 groups, taking stratification factors into account (method of delivery [vaginal route or cesarean delivery] and history of breastfeeding [breastfeeding present at the exit of maternity or not]). This allocation will be managed through the randomization management interface called the Interactive Web Response System (IWRS). All throughout the study, neither the investigator nor the subject will have access to the nature of the product they are testing (double-blind). The product labeling will not show any difference between active and placebo products. The randomization list (allocation of active and placebo batches) will be established by an independent person neither participating in the clinical phase nor processing the study data.

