**Figure 2 F2:**
[figure not shown]
Clinic schedule of the trial.

During the first visit (V1), a face-to-face interview will be conducted with the participant's parents. An investigator (pediatrician) will explain the study procedures in detail, particularly the purpose of the study, the procedures to be undergone, and the potential risks and benefits of participation. The inclusion and exclusion criteria will be reviewed to determine if the participant qualifies for the study. If the parents agree to have their infant enrolled in the trial, one of them will sign an informed consent. At the same time, the investigator will collect relevant information on demography, medical history, and concomitant medications.

During this first visit, parents can choose any brand of milk powder in the list of allowed infant formulas (without probiotics; if with prebiotics, GOS < 2 g/100 g and no FOS inside) presented by the investigators. The investigators will recommend the Biostime Infant Formula (Biostime Inc., Guangzhou, China). If parents are willing to choose the Biostime Infant Formula from the list, they will be provided a free and sufficient supply of the Biostime Infant Formula. The infant's feeding will have to be completely switched to the new infant formula within 1 week (D1-D8).

A saliva sample will be obtained at the site by the investigators at V1 (D1), V2 (D15), and V3 (D44). Parents will be instructed to collect a stool sample of their infant at home at V1 (before starting the new infant formula), V2 (within 24 h before the visit time), and V3.

The infant's diaries will be provided to parents at each visit, and they will be instructed to fill in these diaries daily from D8 to D99 in order to record GI symptoms (Bekkali scale),^[22]^ crying episodes (number and duration), number of stools, compliance (volume of milk of the first feeding bottle actually drunk, planned to be drunk, and regurgitated), and potential concomitant medications. Moreover, a physical examination will be conducted at each visit, and potential adverse events (AEs) will be monitored throughout the trial by the investigators.

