## Discussion

4

In the early stage of life, the composition of the intestinal microbiota undergoes major modifications, mostly influenced by feeding patterns.^[23]^ Intestinal microflora composition differs substantially in breast-fed infants and formula-fed infants because of the differences in composition between human milk and standard infant formula. The breast-fed infant's microbiota is composed of an increased number of *Bifidobacteria* and *Lactobacilli*, whereas the formula-fed infant's microbiota has more *Enterococci* and *Enterobacteria.*^[24,25]^ It is widely accepted that breast-fed infants are often healthier than formula-fed infants and can fight infections better. This difference is considered to be due to breast milk's composition with molecules with antimicrobial activity and prebiotic oligosaccharides with various health benefits.^[26,27]^ In fact, healthy intestinal microflora are essential to infants’ health, and the composition of intestinal microflora could be adapted by consuming probiotics in infancy.^[28]^ Therefore, the first 2 to 3 years of life are the most critical period in which one can intervene to shape the microbiota as best as possible, and so optimize child growth and development.

Numerous randomized controlled trials have shown that the use of probiotic products, including those that are added to commercially available infant formula and other food products for children, is effective in preventing and treating common diseases such as diarrhea and allergy.^[29,30]^ However, little is known about whether probiotics could offer benefits to healthy infants. With the boom of probiotics appearing on the market, the use of probiotic products in the community is becoming more widespread.^[31]^ It is therefore important to provide sufficient scientific evidence for its effectiveness in the digestibility and immunity of exclusively formula-fed healthy infants. An effective, practical, and acceptable intervention for these infants would represent a major clinical and public health advance. If cost effective, the simplicity of the intervention is such that the administration of probiotic supplementation or follow-on formula to infants, given beyond early infancy, may be associated with some clinic benefits. However, it is worth noting that despite there currently being no safety concerns regarding probiotics, more research is required regarding the long-term and routine use of probiotic-supplemented formula to healthy infants.

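### Beyond the 2-week run-in no minimum time since last breast milk is set, and the breastfeeding stratum does not record how recently an infant was weaned (minor)

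*Protocol article*

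**What the plan says.** All references are to the protocol article.

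- **Feeding criterion (3.3 Inclusion criteria):** "Being exclusively formula-fed (no breast milk meal) at the inclusion visit". The time reference is the visit itself.
- **Other exposures (3.3 and 3.4):** these carry look-backs. Antibiotics appear as "No use of antibiotics within 1 month (CCDC" and again as "Oral antibiotic treatment at V1 visit and within 4 weeks before V1". Medication and supplements, including probiotics and prebiotics, are barred "in the 4 weeks preceding the study start". Gastrointestinal disease has a 1-month look-back.
- **Stratification (3.5 Randomization and blinding):** one of the two factors is "history of breastfeeding [breastfeeding present at the exit of maternity or not"; the other is mode of delivery.
- **Run-in (3.1 Design and setting):** "Participating infants will undergo a 2-week run-in period and then be randomly allocated (at a 1:1 ratio". Section 3.7 adds: "The infant's feeding will have to be completely switched to the new infant formula within 1 week (D1-D8".
- **Endpoint and model (3.12 and 2.2):** the primary endpoints are the V3 (D44) minus V2 (D15) changes in seven bacterial groups. The ANCOVA contains product, the V2 value and their interaction, and no feeding-history term.
- **Rationale (4 Discussion):** "Intestinal microflora composition differs substantially in breast-fed infants and formula-fed infants". The same paragraph attributes early changes in the microbiota mostly to feeding. It associates bifidobacteria and lactobacilli with breast-feeding, and enterococci and enterobacteria with formula.

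**The concern.** The plan sets look-backs for several exposures that disturb the gut flora but none for breast milk, which its own Discussion treats as a leading determinant. Entry is at 120 to 180 days of age, so some infants may have left the breast shortly before V1.

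The stratum does not separate them. Among infants breastfed at discharge, one weaned at two weeks and one weaned the day before V1 fall in the same class. The V2 covariate helps only in part, because a single V2 count cannot show whether that count is stable or still moving.

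Two things are at stake: the precision of the primary comparison, and the reading of the within-group V2-versus-V3 tests in 2.3 Secondary analysis, where a drift unrelated to the product counts as change.

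**Working it through.** **1. Overlap with the primary endpoints.** The four groups named in the Discussion cover *B. bifidum*, *B. longum ssp. infantis*, *L. helveticus*, *Enterococcus* and *Enterobacteria*. *C. perfringens* and *Bacteroides* are not among them. That is 5 of 7. The Discussion speaks of broad groups, whereas three of these five endpoints are species or subspecies within them.

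**2. Time off breast milk at baseline.** An infant weaned just before V1 who stays on formula has 15 − 1 = 14 days by V2. An exposure with a 4-week look-back, counted from V1, has at least 28 + 14 = 42 days. The formula switch may run to D8, leaving 15 − 8 = 7 days on the new formula before V2. The endpoint window is 44 − 15 = 29 days.

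**3. No plan figure to reproduce.** Section 3.2 sets 100 per group from a minimum of 50 plus expected drop-out, with no effect size, SD or power. The rest is illustration. Its assumptions are a share *f* of recently weaned infants, whose V2–V3 change is shifted by *m* SD equally in both arms, a true product effect of 0.4 SD and two-sided alpha of 0.05.

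**4. Variance of the change.** The multiplier is v = 1 + f(1 − f)m²:

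| f | m = 0.5 | m = 1.0 |
|---|---|---|
| 5% | 1.01 | 1.05 |
| 10% | 1.02 | 1.09 |
| 20% | 1.04 | 1.16 |
| 30% | 1.05 | 1.21 |

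For example, 0.3 × 0.7 × 1² = 0.21.

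**5. Power**, as Φ(0.4/√(2v/n) − 1.96):

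- n = 100 per group: 80.7% with v = 1, falling to between 80.3% (v = 1.01) and 73.0% (v = 1.21).
- n = 50 per group (the minimum in 3.2): 51.6%, falling to between 51.1% and 44.4%.

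**6. Chance imbalance.** With m = 1 and simple randomisation at 100 per group, the 95% limit of the shift in the group difference is 1.96 × √(2f(1 − f)/100). This is 0.08 SD at f = 10% and 0.13 SD at f = 30%. The standard error of the difference is already √(2/100) = 0.14 SD. This imbalance is the same cost as in step 4 seen another way, so the two must not be added.

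**7. Within-group tests.** The mean drift in each arm is f × m, from 0.05 × 0.5 = 0.025 SD to 0.3 × 1.0 = 0.30 SD. With 100 infants the standard error of a mean change is √(v/100), about 0.10 to 0.11 SD. The drift is therefore about 0.25 to 2.7 standard errors (0.025/0.10 to 0.30/0.11). No concurrent control removes it in these tests.

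**The case against.** The strongest reply is that the design already deals with most of this. The run-in separates the eligibility check from the baseline by two weeks, and the baseline is V2, not V1. Any drift after weaning occurs in both arms, so placebo control separates it from the product effect. Chance imbalance is ordinary sampling error that the p-value already reflects, and the V2 covariate absorbs part of it. All of this stands, and it limits the point to precision and the within-group tests.

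A reader might go further than the document allows in four ways:

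- **That there is no breast-milk washout at all.** The run-in gives at least about 14 days, although it is not labelled as a washout.
- **That the flora is still changing at V2.** The Discussion compares breast-fed with formula-fed infants and gives no time course after weaning. Nothing in the article shows that 14 days is too short, and parity with the antibiotic look-back is only an analogy.
- **That the primary comparison is biased.** Under randomisation the expected bias is zero.
- **That breast milk may be resumed during the run-in.** No sentence expressly bars it and no V2 re-check is described. However, section 3.7 requires a complete switch to the chosen formula by D8, and the Abstract describes the infants allocated after the run-in as exclusively formula-fed. A re-check is the sort of detail that an article leaves to the full protocol.

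The reply does not remove the basic mismatch. Breastfeeding history was judged important enough to be one of two stratification factors, yet the version chosen ignores recency and the printed model has no feeding term.

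**Conclusion.** The point holds as a minor one. Eligibility guarantees about two weeks off breast milk at baseline, and neither the stratum nor the primary model captures time since weaning. Under the assumed ranges (5–30% recently weaned, shift 0.5–1.0 SD) the variance of the change rises by about 1% to 21%. Power at 100 per group falls from 80.7% by between 0.4 and 7.7 percentage points. The V2 covariate would recover part of that, so these are upper figures for each assumption.

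The share and the shift have no source in the article. If few infants are recently weaned, or if the flora settles within two weeks, the cost is close to nil. The within-group tests are the more exposed part, because drift there is not offset by a control. This is a missed opportunity for precision, not an error or contradiction in the plan.

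**What to change.** 1. At the V1 interview, record the date of last breast milk, counting partial feeds, and whether the infant was ever breastfed.
2. Pre-specify time since last breast milk as a covariate in the primary ANCOVA, alongside the V2 value and the two stratification factors, which the printed model does not contain. Fix in advance its functional form and the coding for never-breastfed infants (for example, age at V1).
3. Keep the current IWRS factor. It records early feeding exposure, and the covariate supplies the recency that it lacks.
4. Optionally, if recruitment allows, add a look-back on breast milk comparable to those already set for antibiotics and supplements. This is the sponsor's trade-off: age is capped below 180 days, so some infants who wait would become too old to enter.

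Cost of items 1 to 3: one short addition to the V1 interview and one extra model term for recency, plus one binary term for each stratification factor. If recency turns out not to matter, the loss is about one degree of freedom. Recruitment slows only if item 4 is adopted. The question must be in place before enrolment, because a date recalled later is less reliable.

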### Exclusion criteria

3.4

Infants meeting any of the following criteria will be excluded from the study:♦Congenital illness or malformation.♦Critical prenatal and/or postnatal disease.♦Mothers with metabolic and/or chronic disease.♦An allergic constitution and sensitive to probiotics (CCDC).♦Serious diseases, such as those of the cardiovascular, cerebrovascular, endocrine, liver, kidney, and hematopoietic systems, or mental diseases (CCDC).♦Other drugs during the administration of the study products, thus making it impossible to judge their efficacy and/or influencing the judgment of results (CCDC).♦Current or previous illnesses or conditions or interventions that could interfere with the study (affecting tolerance and/or growth), such as gastrointestinal malformations, chronic diarrhea, malabsorptive syndrome, malnutrition, congenital immunodeficiency, or major surgery, as per the investigator's clinical judgment.♦Oral antibiotic treatment at V1 visit and within 4 weeks before V1.♦Any medication or nutritional supplements (such as probiotics and prebiotics, except for infant formula) in the 4 weeks preceding the study start.♦Having ever consumed the test product.♦Medical conditions for which a special diet other than standard (nonhydrolyzed) cow's milk-based infant formula is required (such as cow's milk allergy, soy protein allergy, fish protein allergy, egg protein allergy, lactose intolerance, and galactosemia).♦Current participation or having participated in another clinical trial during the previous 4 weeks.♦Infants’ legal representatives without the psychological or linguistic capability to sign the informed consent form.♦Reasons to presume that the parents are unable to meet the study plan requirements (e.g., cannot contact the study representatives in the case of emergency, or have a drug addiction).

### Randomization and blinding

3.5

The product allocation list will be generated using a dynamic randomization algorithm designed to minimize an imbalance between the 2 groups, taking stratification factors into account (method of delivery [vaginal route or cesarean delivery] and history of breastfeeding [breastfeeding present at the exit of maternity or not]). This allocation will be managed through the randomization management interface called the Interactive Web Response System (IWRS). All throughout the study, neither the investigator nor the subject will have access to the nature of the product they are testing (double-blind). The product labeling will not show any difference between active and placebo products. The randomization list (allocation of active and placebo batches) will be established by an independent person neither participating in the clinical phase nor processing the study data.

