### Statistical analysis

2.1

Statistical analysis of all data will be performed by a specialized statistician in a blind manner. To estimate the efficacy of this trial, both the intention-to-treat and per-protocol populations will be analyzed. Baseline characteristics will be compared by unpaired Student's *t*-test (parametric test) or Mann–Whitney test (nonparametric test) and chi-square or Fisher's exact test (if one of the expected frequency < 5). All statistical analyses of the data will be performed using SAS software version 9.3 or higher (SAS Institute Inc., Cary, NC), and a *P*-value < 0.05 will be considered statistically significant. The target variables for analysis are as follows.

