### Primary analysis

2.2

The primary endpoints, the V2-V3 changes in *Bifidobacterium bifidum*, *Bifidobacterium longum ssp. infantis*, *Lactobacillus helveticus*, *Clostridium perfringens*, *Enterococcus*, *Enterobacteria*, and *Bacteroides* in stools will be analyzed using the following ANCOVA model (SAS PROC MIXED):

*Y* = Product +Baseline + (Product × Baseline)

where

Y = V2–V3 change in fecal microbiota

Product = study products

Baseline = baseline value (V2)

Product × Baseline = Product − Baseline interaction

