### Participant and eligibility

3.2

Two hundred infants, aged 4 to 6 months, will be included in this study. As no detailed data were available in the literature about the primary endpoint of the present study in the target population of interest, no formal sample size calculation has been performed. To meet the recommendations of the Chinese Center for Disease Control and Prevention (CCDC) (≥ 50 subjects per group) and anticipating a high drop-out rate, it has been decided to include 100 infants in each group of the study. The Committee on Nutrition of the European Society for Paediatric Gastroenterology, Hepatology, and Nutrition (ESPGHAN) has concluded that the administration of probiotic-supplemented infant formula during early life (≤ 4 months of age) does not result in any consistent clinical effects.^[20]^ The World Health Organization (WHO) recommends that infants start receiving complementary foods at the age of 6 months. Thus, the age of 4 to 6 months will be applied for the inclusion of subjects.

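### The primary ANCOVA leaves out the two factors on which allocation is balanced, so it gives up precision to the extent that they predict the outcome beyond the V2 baseline

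*Protocol article*

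**What the plan says.** Section 3.5 of the protocol article (Randomization and blinding) describes dynamic allocation that aims to keep the arms balanced, "taking stratification factors into account (method of delivery [vaginal route or cesarean delivery] and history of breastfeeding" at discharge from maternity. Each factor has two levels. Allocation is 1:1 with 100 infants per group (sections 3.1 and 3.2).

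Section 2.2 (Primary analysis) writes the model out as "Product +Baseline + (Product × Baseline"), defines each term, and names the SAS procedure. The outcome is given as "Y = V2–V3 change in fecal microbiota", for seven organisms. Neither allocation factor appears.

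Section 2.3 applies the same ANCOVA to salivary SIgA, and section 2.5 applies it to growth. The diary outcomes in section 2.3 use a repeated-measures model with product, week and their interaction, again without the factors. No section mentions an adjusted model or a re-randomisation test. On significance, section 2.1 says only that a P-"value < 0.05 will be considered statistically significant". Section 3.2 states that no formal sample size calculation was done and that high drop-out is expected.

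**The concern.** The analysis does not match the allocation scheme. Dynamic balancing keeps the two arms alike on delivery mode and breastfeeding history, so these factors contribute almost nothing to the true sampling variance of the product effect. An ANCOVA that ignores them leaves their variance in the residual, and the model-based standard error is then larger than the true one. Intervals come out wider than the design warrants, and the test rejects a true null hypothesis less often than its nominal 5%.

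What is at stake is efficiency. The trial has no stated power and expects many drop-outs, so there is no demonstrated margin from which to give up precision that the allocation already provides.

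**Working it through.** **Inputs.** From the protocol article: dynamic allocation on two binary factors (3.5); 200 infants, 1:1 (3.1, 3.2); the model in 2.2; a 0.05 threshold (2.1). Sidedness is not stated, so two-sided is assumed. The article gives no power, effect size or standard deviation, so it has no figure to reproduce. Two further assumptions are needed: R², the share of residual variance after the V2 baseline that the two factors explain, and a nominal power of 80% for the stated model, for which effect / model SE = 1.96 + 0.84 = 2.80.

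**Standard error.** With the factors balanced, true SE = model SE × √(1−R²). The stated model's SE is therefore too large by 1/√(1−R²): 1.026 at R² = 0.05, 1.054 at 0.10 and 1.118 at 0.20.

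**Type I error of the stated model.** 2·P(Z > 1.96/√(1−R²)).
- R² = 0.05: 1.96/0.9747 = 2.011, giving 4.4%.
- R² = 0.10: 1.96/0.9487 = 2.066, giving 3.9%.
- R² = 0.20: 1.96/0.8944 = 2.191, giving 2.8%.

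**Power.** The unadjusted estimate already has the smaller true variance, because allocation is balanced. Its power is therefore not the nominal 80% but Φ((2.80−1.96)/√(1−R²)). Adjusted power is Φ(2.80/√(1−R²) − 1.96).

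| R² | Unadjusted | Adjusted | Gain (points) |
|---|---|---|---|
| 0 | 80% | 80% | 0 |
| 0.05 | Φ(0.862) = 80.6% | Φ(0.913) = 81.9% | 1.4 |
| 0.10 | Φ(0.885) = 81.2% | Φ(0.991) = 83.9% | 2.7 |
| 0.20 | Φ(0.939) = 82.6% | Φ(1.170) = 87.9% | 5.3 |

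**Simulation.** Two-factor minimisation was simulated with a 0.9 biased coin and evenly split factors (both assumed), 200 infants and 4,000 runs under the null. The product effect was tested at the mean baseline.
- The stated model's type I error was 4.3%, 4.6% and 2.6% at R² = 0.05, 0.10 and 0.20, with Monte Carlo error of about 0.3 points. At R² = 0 it was 4.6%, close to nominal.
- At R² = 0.20 the mean model SE was 0.158 against an empirical SD of 0.140. Adding both factors brought the SE to 0.142, and over all scenarios the adjusted type I error was 4.1% to 5.8%.
- Under simple randomisation at R² = 0.20, the stated model had 5.7% type I error and its SE (0.158) matched the empirical SD (0.160). The conservatism therefore comes from combining balanced allocation with omission of the factors.
- Where the factors also drove the V2 baseline, type I error at R² = 0.20 was 3.3%, because the baseline term absorbed part of their effect.
- For a difference of 0.4 SD, power was 77% unadjusted against 81% adjusted at R² = 0.10, and 72% against 79% at 0.20. These runs fix the effect relative to the variance left after the factors, so adjusted power stays near 80% and unadjusted power falls. The table instead fixes the stated model's nominal power at 80%. The direction is the same, and the gains are of similar order (3.4 and 6.6 points against 2.7 and 5.3).

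**The case against.** The strongest objection is that the loss is conditional. Both factors date from birth and maternity discharge, while the outcome is a change over four weeks at 4 to 6 months of age. The V2 count may already carry most of what they predict. The documents give no figure; if R² is zero, nothing is lost, and up to 0.10 the type I error stays near 4%. This stands, and it is why the point is stated conditionally.

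It can also be said that covariates are commonly settled in an analysis plan that is not shown. That carries little weight for these two factors, because section 2.2 writes out a complete model with every term defined.

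A reader might go further in four ways that the documents do not support:
- **That the omission invalidates the test or raises false positives.** The direction is the opposite: the test is conservative.
- **That adjusting lifts power from 80% to 82%–88%.** That takes the unadjusted estimate to have the full variance, although balanced allocation has already reduced it. The fair starting point is 80.6% to 82.6%.
- **That the factors were chosen because they shape gut flora.** Section 3.5 gives no reason. The Discussion stresses feeding patterns, which makes some prognostic value plausible, but it does not size it.
- **That the V1 measurement and age belong in the model too.** V2 is the last value before product and a proper baseline. The V1 stool is taken before the formula switch (section 3.7). If correlation decays with time, so that the V1–V3 correlation is the product of the V1–V2 and V2–V3 correlations, V1 adds nothing. Passing the complementary-food age before V3 affects both arms and is a separate matter, with no quantified link to the outcome.

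**Conclusion.** The mismatch between allocation and analysis is real and stated in the text. How much it costs is unknown. Over an assumed 5% to 20% of residual variance explained, the stated model's standard error is 3% to 12% too large, its type I error is about 4.4% to 2.8%, and adjusting gains about 1.4 to 5.3 points of power from an assumed nominal 80%. The figures rest on near-complete balance of the factors, a two-sided 5% test, and the product effect being read at the mean baseline. Confidence is high in the omission and its direction, and limited in its size. Severity is minor: precision is given up, validity is not.

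**What to change.** Add delivery mode and breastfeeding history as fixed effects to the primary ANCOVA, to the SIgA and growth analyses that reuse it, and to the repeated-measures models for the diary outcomes. State in sections 2.2, 2.3 and 2.5 that the models adjust for the factors used in allocation.

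The cost is a change of wording and two model degrees of freedom out of up to 200 infants. No new data are needed, since the allocation system must already hold both factors for every randomised infant. If the factors prove to predict nothing, almost nothing is lost: at R² = 0 the simulated power for a difference of 0.4 SD was 81% with and without them.
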